## Methods/design

Primary outcomes of interest in this study are the prevalence of KTD and the association of polymorphisms in selected candidate SNPs in genes encoding tubular transporters and *APOL1* with KTD. Secondary outcomes include the presence of elevated retinol binding protein (RBP) levels (defined as retinol-binding protein/creatinine ratio > 2.93 μg/mmol) [25] and urinary N-acetyl-beta-D-glucosaminidase (NAG) levels (NAG > 5.93 U/g Cr).

### Study design

The prevalence and pharmacogenetics of TDF nephrotoxicity in adult PLWHIV in south-western Nigeria is a cross-sectional study with a case control sub-study of PLWHIV who are receiving TDF regimens attending anti-retroviral (ART) clinics in south-west Nigeria. This study will determine the prevalence of KTD in PLWHIV-I and II taking TDF in Nigeria. It will investigate the association of demographic (age, gender), lifestyle (BMI, smoking), concomitant medications (NSAIDs, protease inhibitors, traditional/herbal medicines) and concomitant illness (diarrhoeal disease, tuberculosis, pneumonia, hypertension, diabetes mellitus, HBV/HCV co-infection, etc.) with the development of TDF-induced KTD. This study will also explore whether polymorphisms in the *ABCB1, ABCC2, ABCC4, ABCC10, SLC22A6, SLC22A11* and *APOL1* genes are associated with KTD in PLWHIV in Nigeria treated with TDF, and explore the association between polymorphisms in genes encoding renal drug transporters and levels of urinary RBP as well as NAG in Nigerian PLWHIV treated with TDF. Recruitment into the study commenced in October 2019 and as of June 2020, 2491 participants have been enrolled.

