**Methods:**

This study has two phases. An initial cross-sectional study will screen 3000 individuals attending the HIV clinics in south-west Nigeria for KTD to determine the prevalence and risk factors. This will be followed by a case-control study of 400 KTD cases and 400 matched controls to evaluate single nucleotide polymorphism (SNP) associations. Data on socio-demographics, risk factors for kidney dysfunction and HIV history will be collected by questionnaire. Blood and urine samples for measurements of severity of HIV disease (CD4 count, viral load) and renal function (creatinine, eGFR, phosphate, uric acid, glucose) will also be collected. Utility of urinary retinol binding protein (RBP) and N-acetyl-beta-D-glucosaminidase (NAG) levels as surrogate markers of KTD will be evaluated. Genomic DNA will be extracted from whole blood and SNP analyses performed using the rhAMP SNP genotyping assays. Statistical analysis including univariate and multivariate logistic regression analyses will be performed to identify factors associated with KTD.

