According to 2020 data, 89% (comprising of 55% adults and 35% children) of those with a HIV positive diagnosis in Nigeria are accessing ART, and out of these, 42% were virally suppressed [1, 10]. Tenofovir disoproxil fumarate (TDF) is one of the most frequently used ART [11]. Currently, more than 80% of PLWHIV in Nigeria were receiving a TDF-based regimen, as Nigeria adopted TDF-based ART as the first-line treatment for HIV in 2014 [1, 12]. Whilst the initial randomised control trials suggest good overall safety for TDF, numerous subsequent studies have shown issues with the renal safety profile, including KTD in various study settings [13]. Furthermore, TDF has also been associated with a wide range of other manifestations of renal impairment than KTD such as low eGFR and rapidly declining eGFR. Globally, the reported incidence of TDF-induced nephrotoxicity ranges between 0.7 and 22% [14, 15]. Likanonsakul et al. [16] in their study reported that approximately 20% of PLWHIV receiving TDF in Thailand had β2-microglobulinuria, a marker of tubular dysfunction. Various risk factors have been associated with KTD including co-morbidities (such as hepatitis C, diabetes mellitus), low body weight, older age, concomitant administration of potentially nephrotoxic drugs, low CD4 count and duration of therapy [17].

In West Africa, a study carried out among a Ghanaian population of PLWHIV taking TDF showed that the prevalence of creatinine clearance less than 60 ml/min/1.73m^2^, dipstick proteinuria and asymptomatic renal tubular dysfunction was 7, 37 and 15% respectively [18]. In Nigeria, little is known about the prevalence of TDF-induced KTD. It is difficult to screen for this complication in resource-poor settings, and very few Nigerian studies have investigated markers of TDF-induced KTD. A study of 57 PLWHIV in Port Harcourt in southern Nigeria suggested an increased burden of KTD in individuals exposed to the TDF regimen. Results showed that after 12 weeks of exposure, 14% of PLWHIV exposed to TDF developed phosphaturia [19].

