### Recruitment of participants

An outline of how participants will be recruited for this study is shown in the study flow chart in Fig. 2. After obtaining patient consent, case report forms will be completed for all participants and will include the following data:
Demographics - Age, sex, body weight, body mass indexPast medical history - history of AIDS, route of HIV transmission, specific combination of ART, duration of therapy, history of tobacco use, hypertension, diabetes mellitus, congestive cardiac failure, co-infection with hepatitis B and C, concurrent use of ritonavir-boosted protease inhibitors, concurrent use of nephrotoxic drugs, such as ganciclovir and sulfamethoxazole/trimethoprim.Baseline laboratory data - CD4 count, HIV viral load, serum creatinine and estimated glomerular filtration rate (eGFR). As recommended by the National Kidney Foundation, eGFR will be calculated using the CKD-EPI formula [31].

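### The plan relates current-status factors to the development of KTD, but a single enrolment records them together with prevalent KTD, so their order cannot be established

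*Protocol article*

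**What the plan says.** Under Study design, the article says the study "is a cross-sectional study with a case control sub-study of PLWHIV" on TDF regimens. The same section lists the exposures of interest as age, gender, "lifestyle (BMI, smoking), concomitant medications (NSAIDs, protease inhibitors, traditional/herbal medicines) and concomitant illness", and relates them "with the development of TDF-induced KTD". CD4 count is not in that list. It appears in the Background, where the literature's risk factors include "low body weight, older age, concomitant administration of potentially nephrotoxic drugs, low CD4 count and duration of therapy". The Abstract also describes "Blood and urine samples for measurements of severity of HIV disease (CD4 count, viral load") among the samples to be collected.

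On timing, Recruitment of participants states: "After obtaining patient consent, case report forms will be completed for all participants". The laboratory items there are headed "Baseline laboratory data - CD4 count, HIV viral load, serum creatinine and estimated glomerular filtration rate (eGFR"). Setting and study population requires at least 3 months of follow-up on TDF and a viral load below 200 copies/ml, and takes creatinine for eGFR from the month of enrolment.

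Statistical analysis plans logistic regression for factors associated with KTD, with univariately significant factors passed to a stepwise model. Strengths and limitations concedes the lack of longitudinal data, but only for KTD progression.

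**The concern.** *Development* implies that the exposure came before KTD. Here both are read at one time point, after treatment has started and viral suppression has been reached. An enrolment weight or CD4 count may reflect recovery on treatment, a consequence of KTD, or the state before KTD arose, and the plan names nothing that would separate these. The same holds for a medicine or acute illness that is current at enrolment. The laboratory values called baseline are enrolment values, which invites reading them as pre-exposure.

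The Discussion intends the results to inform prevention and clinical programmes. Correlates of prevalent KTD could be reported there as its causes, and a real effect of low weight or low CD4 count at TDF start could be misjudged in either direction.

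**Working it through.** **1. Timing, from the documents.**
- Time to toxicity: the article cites a median of 3.6 months after TDF start in one place and about 3 months in another.
- Time on TDF: TDF became first-line in 2014 and recruitment began in October 2019. Someone who started in 2014 would have had about 2019 − 2014 = 5 years on TDF. The distribution of TDF duration is not given.
- KTD onset: no date is named, so KTD may long predate the enrolment measurements.
- Start values: no pre-TDF or nadir CD4 count and no pre-TDF weight is named.

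**2. The plan's own figures.** There is no power or sample size figure for the non-genetic factors. The figures that exist reproduce and are not in question. For an odds ratio (OR) of 1.75, a 1:1 matched calculation (carrier frequency 1 − 0.81² = 0.3439, prevalence 13%, two-sided alpha 0.003, power 80%) gives 397 per group against the stated 398. Screening needs 400/0.13 = 3077 against approximately 3000.

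**3. Simple dilution (assumed correlations).** If the pre-TDF value alone matters and the enrolment value is a noisy copy with correlation r, then observed log OR ≈ r × true log OR, so observed OR = (true OR)^r.

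| True OR per SD | r = 0.3 | r = 0.5 | r = 0.7 |
|---|---|---|---|
| 1.5 | 1.13 | 1.22 | 1.33 |
| 2.0 | 1.23 | 1.41 | 1.62 |

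For positive r this formula can only shrink an OR towards 1. It cannot reverse one.

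**4. Allowing KTD to affect the factor (simulation, all inputs assumed).** *Low* means the lowest 30%, KTD prevalence is 13%, and the true OR for a low pre-TDF value is 2.0.

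| Effect of KTD on the enrolment value | r = 0.8 | r = 0.6 | r = 0.4 |
|---|---|---|---|
| None | 1.52 | 1.33 | 1.20 |
| Lowers it by 0.1 SD | 1.78 | 1.56 | 1.40 |
| Lowers it by 0.3 SD | 2.43 | 2.16 | 1.95 |

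The observed OR can fall on either side of the true 2.0.

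**5. Allowing recovery over time on TDF (simulation, all inputs assumed).** True OR 1.75, weight of 0.6 on the pre-TDF value, and TDF duration uniform from 0.25 to 6 years.

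| KTD odds per year on TDF | Recovery per year | Crude OR | OR adjusted for TDF duration |
|---|---|---|---|
| ×1.0 | 0.3 SD | 1.22 | 1.25 |
| ×1.2 | 0.15 SD | 1.11 | 1.29 |
| ×1.2 | 0.3 SD | 0.96 | 1.25 |
| ×1.4 | 0.15 SD | 1.01 | 1.30 |
| ×1.4 | 0.3 SD | 0.81 | 1.28 |

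Reversal appears only in the crude OR. After adjustment for duration the OR is diluted but keeps its direction.

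**6. Where duration is handled.** Cases and controls are matched on TDF duration within 3 months, but the 3000-person phase is unmatched. The adjustment set named under Statistical analysis, given for the allele and haplotype analysis, includes duration of HIV infection and not TDF duration. Because univariate significance is the entry rule, a factor whose crude OR is masked by duration could be dropped before any adjustment.

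**The case against.** The strongest reply is that this is the ordinary caveat of any cross-sectional study. The design is openly labelled, and the Abstract and Statistical analysis speak only of factors associated with KTD. Even the Study design sentence is framed as association, so one word is at fault. The primary outcomes are prevalence and SNP associations, which exposure timing does not touch. All of that stands and limits the weight of the point. It does not remove it: risk factors are a stated aim, the wording promises more than the design gives, and the stated limitation does not cover temporal order.

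Four stronger readings are tempting and are not supported:
- *The CD4 and weight odds ratios are diluted or reversed.* Neither is established. Inflation is also possible, and reversal needs further conditions that adjustment for, or matching on, TDF duration largely removes.
- *CD4 count is part of the development objective.* It is a literature risk factor in the Background and a collected variable, but it is absent from the Study design list.
- *Every medicine and illness is purely concurrent.* History of AIDS, ART combination, duration of therapy, tobacco, hypertension, diabetes and hepatitis B/C are recorded as history and may predate KTD.
- *The clinic records are known to hold start values.* The exclusion criteria require treatment status, ART start date and ART combination. They do not require CD4 count or weight at start, and ART start need not be TDF start.

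**Conclusion.** The point holds for current-status factors: weight or BMI, CD4 count, NSAIDs, herbal medicines and acute illness. Their order relative to KTD cannot be established, so the study can report association with prevalent KTD but not with its development. Their odds ratios may be diluted, inflated or, without adjustment for TDF duration, reversed. The documents determine neither size nor direction. The figures above (1.20 to 2.43 for a true 2.0; crude 0.81 to 1.22 for a true 1.75) only illustrate the range. They rest on assumed correlations, recovery rates and effects of KTD on the factor.

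Items recorded as history, the genotype analyses, the prevalence estimate and the sample size are not affected. The change is worth making because it serves the study's own risk-factor aim at modest cost.

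**What to change.** - In Study design, replace the reference to development with association with prevalent KTD.
- In Strengths and limitations, extend the missing-longitudinal-data limitation to say that the order of exposure and KTD cannot be established for current-status factors.
- Where clinic records hold them, abstract body weight and CD4 count nearest before TDF start and use these as the risk-factor variables. Keep the enrolment values as descriptors, and label them as enrolment values.
- Include TDF duration in the risk-factor model for the unmatched 3000-person phase, whatever its univariate p-value.
- Record start dates of medicines and illnesses relative to TDF start where available. A start before the survey month should not count as evidence of order: KTD onset is unknown, and a medicine begun after onset would still qualify.

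Cost: two wording changes, one model term and chart abstraction. The abstraction would be largely retrospective, since 2491 participants had been enrolled by June 2020. The share of missing start values is unknown, and a stated way of handling them is needed.

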### Setting and study population

The study will be conducted at the Department of Internal Medicine, Ladoke Akintola University of Technology Teaching Hospital (LTH), Osogbo, Nigeria and the Department of Internal Medicine Research Laboratory, University of the Witwatersrand, Johannesburg, South Africa. Participants will be recruited from ART clinics in Nigeria including LTH (Osogbo), Jaleyemi Catholic Hospital (Osogbo), Osun State Hospitals (Asubiaro, Ede, Ikire, Iwo, and Ila Orogun), Adeoyo State Hospital (Oyo State) and Seventh Day Adventist Hospital (Ile-Ife).

For the case-control phase of the study, PLWHIV on a TDF regimen under regular follow up for at least 3 months at the ART clinics who developed proximal KTD will be designated as cases. Research has shown that the median time to nephrotoxicity after TDF initiation is 3.6 months [8], hence, the rationale for a minimum of 3-months on TDF. The controls will be PLWHIV on a TDF regimen under regular follow up for ≥3 months at the ART clinics showing none of the abnormalities suggesting proximal KTD. The cases will be matched one-to-one to controls by gender, age (+/− 5 years), and TDF duration (+/− 3 months) and will be done on an ongoing basis during recruitment of study participants.

Participants meeting the inclusion criteria will be PLWHIV, aged 18 years and above, receiving TDF-containing therapy, on regular follow up for a minimum of 3 months with a viral load of less than 200 copies/ml. The rationale for the use of 3 months cut off point for the duration of tenofovir treatment was based on the results of a previous study by Brennan et al. [8] that showed that the median time to nephrotoxicity after initiation of TDF was approximately 3 months.

The following individuals will be excluded from the study: Individuals with incomplete history of antiretroviral treatment, including HIV treatment status (either treatment-naïve or experienced), date of commencement of ART and combination of ART); persons who are pregnant or lactating; persons with an estimated glomerular filtration rate (eGFR) < 60 ml/min/1.73m^2^ (eGFR will be calculated by Chronic Kidney Disease Epidemiology Collaboration [CKD-EPI] from serum creatinine estimated during the month enrolled in the study); persons with glomerulonephritis, including IgA Nephropathy and Lupus Nephritis; heart failure (NYHA 3 & 4), malignancy and non-Nigerians.

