### Sample size and power analysis

At least 3000 participants will be recruited for the cross-sectional study from which 400 cases and 400 matched controls will be selected for the case-control sub-study. The sample size was calculated based on the following assumptions. Utilising 1000 Genomes data, we estimated the minor allele frequency (MAF) within the population, using the Yoruba in Ibadan (Nigeria) as a proxy for our study population [26]. The rare polymorphism, rs9349256 has the lowest MAF of 0.01 while the common polymorphism, rs717620 has the highest MAF of 0.42, the average MAF being 0.19. In addition, a Bonferroni correction was incorporated by setting our alpha level at 0.003 (0.05/18) to account for the multiple comparison testing. With the aid of a web browser program for basic sample size calculations of single nucleotide polymorphism (SNP) studies [27–29] [http://biostats.usc.edu/Quanto.html] and using a dominant inheritance model, the average MAF of 0.19, 13% KTD prevalence [30], a power of 80% and an alpha of 0.003, a sample size of 400 cases and 400 controls is able to detect a minimum odd ratio (OR) of 1.75 (case control phase). Table 1 indicates the required sample size (per group using a dominant model) to detect different odds ratios. Based on the data from a previous study in Nigerian PLWHIV which reported the prevalence of TDF-induced KTD as 13%, we made an assumption that 13% of TDF-treated individuals will develop KTD [30]. Therefore, taking this into consideration, the number needed to be screened to identify 400 cases is approximately 3000. We will therefore screen 3000 participants in the cross-sectional phase of this study.

**Table 1 Tab1:** Calculations of the sample size (per group using a dominant model), required to detect different odds ratios in case-control analysis, assuming alpha = 0.003; power = 80% and ratio cases/controls = 1

Odds ratio	Sample Size (N)
1.25	2531
1.50	760
1.75	398
2.00	260
2.25	191
2.50	150
2.75	124
3.00	106

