### Statistical analysis

Descriptive results of continuous variables will be expressed as medians and interquartile ranges. Continuous variables will be tested for normality using the Shapiro–Wilk test and compared using the student’s *t* test or Wilcoxon rank sum test, as required. For the comparison of proportions, the Chi-square test will be used, with Fisher’s corrections applied when needed. Multivariate logistic regression analyses will be performed to identify factors associated with KTD. Parameters with significant *p*-values in the univariate analysis will be entered into a stepwise multivariate analysis. Deviations from Hardy-Weinberg equilibrium of individual alleles and differences in allele frequencies between the two groups will be evaluated by either the chi-square test or Fisher’s exact test where appropriate. Statistical comparisons for genotype frequencies between persons with KTD and those without KTD will be made by the chi-square test or Fisher’s exact test. Associations between allele sets or haplotypes and the risk of TDF-induced KTD will be estimated by computing odds ratios and 95% confidence intervals from multivariable logistic regressions. This analysis will include adjustments for demographic characteristics (age, sex, and BMI), baseline eGFR, duration of HIV infection, protease inhibitor therapy, and other antiretroviral treatment. All statistical analyses will be conducted using Stata 12 and R statistical software. *P* values < 0.05 will be considered statistically significant. Methods for controlling the false discovery rate and Bayesian analysis under shrinkage priors will be used when reporting the results of multivariable logistic regression.

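### Recruiting clinic and ethnic group are missing from the matching and the SNP adjustment set, and clinic from the risk-factor model, leaving associations open to confounding

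*Protocol article*

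**What the plan says.** **Recruitment.** Under Setting and study population: "Participants will be recruited from ART clinics in Nigeria". Nine clinics are named, among them a teaching hospital, mission hospitals and state hospitals. Eligibility restricts by nationality only: the exclusions end with "heart failure (NYHA 3 & 4), malignancy and non-Nigerians".

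**Matching.** "The cases will be matched one-to-one to controls by gender, age" (within 5 years) and TDF duration (within 3 months). Clinic and ethnic group are not matching factors. Matching is done continuously as recruitment proceeds.

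**Models.** Under Statistical analysis, the list for the allele and haplotype models is "adjustments for demographic characteristics (age, sex, and BMI), baseline eGFR, duration of HIV infection, protease inhibitor therapy, and other antiretroviral treatment". The risk-factor model is separate: variables significant on univariate testing go into a stepwise procedure. Clinic is not among the candidate factors listed under Study design.

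**Allele frequencies.** The sample-size section takes them from 1000 Genomes, "using the Yoruba in Ibadan (Nigeria) as a proxy for our study population".

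**Target of the prevalence estimate.** Study design states the aim as the prevalence of KTD among people taking TDF in Nigeria, which is wider than the nine clinics. It also reports 2491 participants enrolled by June 2020.

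**The concern.** Both primary outcomes are affected.

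- **Associations.** If KTD frequency differs between clinics, through case mix, referral or local practice, any exposure that also differs between clinics will look associated with KTD in a pooled model. Protease-inhibitor and herbal-medicine use are factors that could differ in this way. Matching on gender, age and TDF duration does not prevent it, because a case may be paired with a control from any clinic.
- **SNPs.** Allele frequencies can differ between ethnic groups. If KTD risk does too, a SNP with no effect shows an association. The Hardy-Weinberg check does not adjust for this, and no other safeguard is stated.
- **Prevalence.** An interval that treats 3000 people as independent describes these clinics. It does not carry between-clinic variation into a statement about a wider population.

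**Working it through.** **1. The plan's own figure.** With MAF 0.19 and a dominant model, the carrier frequency is 1 − 0.81² = 0.344. For OR 1.75 and 13% prevalence, carriers are 45.9% of cases and 32.7% of controls. The two-sided two-proportion formula at 80% power gives 393 per group at alpha 0.003, and 398 at the unrounded 0.05/18. Table 1 gives 398. The sample size reproduces, so this point exposes no arithmetic error.

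**2. Prevalence interval.** Inputs from the article: N = 3000, prevalence 13%, nine clinics. Assumed: equal clinic sizes (3000/9 = 333) and the intraclass correlation (ICC).

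Design effect = 1 + (333.3 − 1) × ICC. Half-width = 1.96 × √(0.13 × 0.87 × design effect / 3000).

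SD of clinic prevalence = √(ICC × 0.13 × 0.87). With nine clinics, the t multiplier on 8 df (2.306) replaces 1.96 in the last column.

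| Assumed ICC | SD of clinic prevalence (points) | Design effect | Half-width (points) | Half-width with t, 8 df |
|---|---|---|---|---|
| 0 | 0 | 1.00 | 1.20 | 1.42 |
| 0.001 | 1.1 | 1.33 | 1.39 | 1.63 |
| 0.005 | 2.4 | 2.66 | 1.96 | 2.31 |
| 0.01 | 3.4 | 4.32 | 2.50 | 2.94 |

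At ICC 0.005 a simple 95% interval would cover the wider-population prevalence about 77% of the time, and at 0.01 about 65%. At ICC 0 there is nothing to correct.

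**3. Risk factors.** A simulation used nine clinics of 333, baseline prevalence 13%, a clinic effect with SD 0.30 on the log-odds scale, and 1,500 runs. That SD corresponds to 0.30 × 0.13 × 0.87 = 0.034, or ICC about 0.01. The exposure had no effect. A pooled test at nominal 0.05 rejected in:

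- 0.054 of runs when the exposure was unrelated to clinic;
- 0.088 when 10% of its variance lay between clinics;
- 0.37 when it was a pure clinic-level factor.

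**4. SNPs.** Take two ethnic groups and a null SNP, with 400 cases and 400 controls. Carrier frequency in each arm is the mixture of the two groups' carrier frequencies. The test statistic is shifted by (case − control carrier frequency) / standard error. Everything except the 0.19 and the 400 per arm is assumed.

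| Second group's share, cases vs controls | MAF, second vs main group | Carriers, cases vs controls | Spurious OR | Error at 0.003 | Error at 0.05 |
|---|---|---|---|---|---|
| 15% vs 10% | 0.24 vs 0.19 | 35.6% vs 35.2% | 1.02 | 0.0032 | 0.052 |
| 30% vs 15% | 0.29 vs 0.19 | 39.0% vs 36.7% | 1.10 | 0.011 | 0.10 |
| 46% vs 27% | 0.35 vs 0.19 | 45.2% vs 40.8% | 1.20 | 0.044 | 0.24 |

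The last row is what follows if 30% of participants belong to the second group and their KTD prevalence is 22% against 11%. The 0.05 column is shown because Statistical analysis states that threshold, while the sample size uses 0.003.

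**The case against.** Several counter-arguments have force.

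- **The prevalence interval.** A reader might infer that the reported error bars are simply too narrow. The documents do not support that. They give no ICC and do not say how the interval is computed, which an article may leave to the full plan. If the nine clinics are treated as fixed strata, the simple interval is not too narrow. The clinics are also not described as a random sample, so a design effect would not make them representative. What stands is conditional: the aim is worded for Nigeria, and for that target clinic variation belongs in the interval.
- **Which text governs what.** The matching and the adjustment list belong to the case-control and genetic analysis. They say nothing about the prevalence interval, and the adjustment list does not bind the risk-factor model.
- **Individual-level exposures.** The factors under Study design are mostly individual-level, and for a factor unrelated to clinic the pooled test is close to nominal. Confounding by clinic is the main danger, rather than standard errors that are too small across the board.
- **Population structure.** Recruitment is confined to Nigerians in the south-west, which limits structure without excluding it. Large inflation needs a sizeable second group, a large allele-frequency gap and nearly doubled KTD risk together. Even then the spurious OR of 1.20 is well below the 1.75 that the study is powered to detect. A reader should not infer that the SNP results will be seriously biased.
- **Ethnic group may be recorded.** The Abstract mentions a questionnaire on socio-demographics. The case report form list under Recruitment of participants omits NSAIDs and herbal medicines, which the study plans to analyse, so it is not exhaustive. It cannot be said that ethnic group is not collected.
- **Feasibility.** Matching runs alongside recruitment, and 2491 people were already enrolled. Re-matching on clinic is not a cheap request.

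The limitations section concedes unmeasured confounding in general terms. That does not answer the point on clinic, which is known for everyone.

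**Conclusion.** The point holds as an avoidable exposure to confounding. The article states its matching factors and SNP covariates explicitly and omits clinic and ethnic group from both. Its risk-factor procedure gives clinic no place. Followed as written, participants from nine clinics are analysed as one population.

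The size cannot be fixed from the documents. For SNPs, the error rate at 0.003 ranges from essentially nominal (0.0032) to a few percent (0.044) over the assumed mixes, and a modest effect is the more likely. For risk factors, the effect is negligible unless the exposure varies by clinic. For prevalence, the half-width goes from 1.2 points to about 1.4, 2.0 or 2.5 at ICCs of 0.001, 0.005 or 0.01. That holds only if prevalence varies by clinic and the inference reaches beyond these nine.

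**What to change.** 1. **Force clinic into the SNP and risk-factor logistic models** as a fixed effect, outside the stepwise selection. It costs 8 degrees of freedom, which 400 cases (50 per clinic term) can support, and needs no new data.
2. **Report prevalence by clinic.** Give an overall interval that allows for between-clinic variation with a small-cluster correction, such as t on 8 df. Alternatively, state that the inference is limited to these clinics and keep the simple interval.
3. **Use self-reported ethnic group in the SNP models** where it is already recorded or can be obtained at a routine visit. Either adjust for it or repeat the analysis in the largest group as a sensitivity analysis. State how many participants lack it.
4. **Do not re-match on clinic.** The model term does the work without disturbing the matching already under way.

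The cost is a few degrees of freedom and possibly a wider prevalence interval.

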This study aims to establish the burden and risk factors for TDF-induced KTD in Nigerians, and explore associations between KTD and polymorphisms in the renal transporter genes as well as *APOL1* risk variants. The study may potentially engender an approach for prevention as well as stemming the burden of CKD in sub-Saharan Africa particularly Nigeria, where GDP per capita is low and budgetary allocation for health is inadequate.

We hypothesise that KTD is common among adult PLWHIV in Nigeria who are receiving TDF-based antiretroviral therapy, and additive contributions from polymorphisms in kidney tubular transporters as well as *APOL1* genetic variants may be associated with the risk of KTD in Nigerians treated with TDF. Further, we hypothesise that the additive contribution from *APOL1* risk alleles would predispose to and enhance the severity of TDF toxicity and that the concomitant use of protease inhibitor may additively influence the susceptibility for severe TDF-induced nephrotoxicity. This paper describes the design and methodology for this study that aims to determine the prevalence and risk factors for TDF-induced KTD in PLWHIV in Nigeria.

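### The viral load < 200 copies/ml entry rule confines the prevalence survey to virally suppressed patients, but the prevalence outcome and burden aim are stated for all TDF-treated people with HIV

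*Protocol article*

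**What the plan says.** **Entry rule.** The section Setting and study population first defines cases and controls for the case-control phase. It then gives inclusion criteria for participants in general: adults on TDF-containing therapy, "on regular follow up for a minimum of 3 months with a viral load of less than 200 copies/ml". The exclusions that follow are from the study as a whole. Under Sample size and power analysis, the 400 cases and 400 controls are drawn from the 3000 surveyed. Nothing confines the viral-load rule to the sub-study.

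**Stated target.**
- Methods/design: "Primary outcomes of interest in this study are the prevalence of KTD", with SNP association as the other primary outcome. No population limit is attached.
- Study design: "This study will determine the prevalence of KTD in PLWHIV-I and II taking TDF in Nigeria".
- Background, aim: "This study aims to establish the burden and risk factors for TDF-induced KTD in Nigerians".
- Background, hypothesis: "KTD is common among adult PLWHIV in Nigeria who are receiving TDF-based antiretroviral therapy".
- Abstract, Methods: 3000 HIV clinic attenders in south-west Nigeria are to be screened for prevalence and risk factors, with no viral-load condition.

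**Where suppression appears.** The Discussion describes a population with suppressed viral load when it explains the risk-factor aim. Strengths and limitations does not mention it. The Background says of those on ART in Nigeria: "out of these, 42% were virally suppressed".

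**The concern.** A prevalence estimate describes the population that could enter the sample. Here that is narrower than the population named in the outcome, aim and hypothesis, and the narrowing is on a characteristic that may not be neutral for KTD. By the article's own account, HIV infection raises the risk of renal impairment, HIV-associated nephropathy involves tubular damage, and a low CD4 count is a KTD risk factor. These suggest more KTD among unsuppressed patients. Poorer adherence, and so lower TDF exposure, could act the other way. A larger sample settles neither the direction nor the size.

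What is at stake is the label on a primary result. As the plan is worded, a prevalence with a narrow confidence interval would be reported as the burden among Nigerians on TDF, although it was measured only in the suppressed part of that group. The public-health argument in the Discussion would rest on it.

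**Working it through.** **1. The plan's own figure.** Sample size and power analysis assumes 13% KTD among TDF-treated individuals and needs 400 cases. 400 / 0.13 = 3,077, against approximately 3000 stated; 3000 x 0.13 = 390 expected cases. The figure reproduces to within 3%. It uses no viral-load information, and the 13% is applied to TDF-treated individuals, not to suppressed ones.

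**2. Sampling error of the survey.** The 95% half-width at 13% and n = 3000 is 1.96 x sqrt(0.13 x 0.87 / 3000) = 0.0120, about 1.2 percentage points.

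**3. What the survey can identify.** Let s be the suppressed share of TDF users, p1 the KTD prevalence among the suppressed and p0 that among the unsuppressed. Then

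overall prevalence = s x p1 + (1 - s) x p0.

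The survey estimates p1 only. Reporting p1 as the overall prevalence gives an error of (1 - s) x (p1 - p0). Neither s nor p0 for these clinics is given in the article, so the overall value needs an outside assumption.

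**4. Size of difference that matters.** The error equals the 1.2-point half-width when |p0 - p1| = 1.2 / (1 - s):

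| Suppressed share s | Source | Difference needed |
|---|---|---|
| 42% | Background, national, all ART | 1.2 / 0.58 = 2.1 points |
| 80% | assumption | 1.2 / 0.20 = 6 points |
| 90% | assumption | 1.2 / 0.10 = 12 points |

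**5. Illustration.** With p1 = 13% and assumed values of p0, the overall prevalence (with the error of the suppressed-only figure, in points) is:

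| p0 (assumed) | s = 42% | s = 80% | s = 90% |
|---|---|---|---|
| 8% | 10.1% (+2.9) | 12.0% (+1.0) | 12.5% (+0.5) |
| 13% | 13.0% (0) | 13.0% (0) | 13.0% (0) |
| 16% | 14.7% (-1.7) | 13.6% (-0.6) | 13.3% (-0.3) |
| 20% | 17.1% (-4.1) | 14.4% (-1.4) | 13.7% (-0.7) |

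For example, 0.42 x 13% + 0.58 x 16% = 14.7%. At 42% suppressed, all three non-zero errors exceed 1.2 points. At 80% or 90%, only one of the six does.

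**The case against.** **The restriction is deliberate and disclosed.** The Discussion says the study was designed around suppressed patients without pre-existing kidney impairment, after noting how hard it is to attribute KTD to TDF alone. Excluding viraemic patients may help that attribution in the survey as well as in the genetic comparison. This stands as a reason to keep the rule. It does not repair the prevalence outcome, because the disclosure is tied to the risk-factor aim and the aim and hypothesis remain unrestricted.

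**The rule does not demonstrably remove more than half of the target.** A reader might infer this from the 42%. That figure is national, covers adults and children on any ART, and comes without a suppression threshold. The surveyed group is adults on TDF with at least 3 months of regular follow-up at named clinics. The article gives no suppressed share for them, and it may well be higher. This objection stands in full.

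**The reported interval need not miss the true overall value.** The unsuppressed prevalences in the illustration are assumptions, and equal prevalence gives no error. The documents support saying that the interval could miss, not that it usually would.

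**No test of viral load is announced.** A reader might infer that the plan tests viral load as a risk factor and has ruled out a result in advance. Viral load is collected as a severity measure (Abstract; Recruitment of participants), but it is in neither the factors named under Study design nor the adjustment list under Statistical analysis. What stands is narrower: variation within 0-199 copies/ml cannot inform a comparison of suppressed with unsuppressed patients.

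**Conclusion.** The point holds as a mismatch between the population that can enter and the population named in the prevalence outcome, burden aim and hypothesis. This follows from the article's text alone and needs no assumption about suppression rates. The survey can estimate KTD prevalence among virally suppressed adults on TDF at its clinics. It cannot identify prevalence among all TDF users.

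How much this matters numerically is unknown. The thresholds of about 2, 6 and 12 points take the planning value of 13% among the suppressed, n = 3000, and suppressed shares of 42%, 80% and 90%, of which only the first is in the article, and for a different population. Neither a bias of a given size nor its direction should be claimed.

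**What to change.** 1. Restate the prevalence outcome, the hypothesis and the conclusion as KTD among virally suppressed (< 200 copies/ml) adults on TDF at the study clinics, in the Abstract, Background, Methods/design and Study design.
2. Report how many TDF-treated attendees were excluded for viral load, so that readers can judge the suppressed share at these clinics.
3. Add the restriction to Strengths and limitations.
4. Do not interpret viral load within this sample as evidence on suppressed versus unsuppressed patients.

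The cost is a narrower claim and a screening log. No new measurement is needed, and recruitment already completed is unaffected, although exclusions before the log starts may have to be recovered from clinic records or reported as unknown.

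Opening the remaining places to unsuppressed patients is tempting but a poor trade. With 2491 enrolled by June 2020, 3000 - 2491 = 509 places were left. If 42% were suppressed, 0.58 x 509 = 295 would be unsuppressed. At an assumed 16% KTD, the half-width in that stratum is 1.96 x sqrt(0.16 x 0.84 / 295) = 4.2 points, too wide to show a 3-point difference from 13%. Eligible cases would fall from 390 to (2491 + 214) x 0.13 = 352, further below the 400 planned, and the entry rule would change mid-survey.
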